## Abstract

**Background:**

In an oligometastatic setting, metastasis-directed treatment could render patients disease free, possibly for a protracted interval. Stereotactic ablative radiotherapy (SABR) is one of the treatment modalities that can be offered to these patients. In addition, the radiobiological qualities of SABR are promising for the use in perceived radioresistant tumours. There is also emerging evidence that SABR can stimulate the immune response, and a specific therapeutic window may exist for the optimal use of radiotherapy as an immune adjuvant. However, when SABR is considered for non-spine bone or lymph node metastases, the optimal fractionation schedule is not yet known.

**Methods:**

The DESTROY-trial is a non-randomized prospective phase I trial determining a regimen of choice for patients with non-spine bone and lymph node metastases. A total of 90 patients will be included in three different treatment regimens. They will be offered stereotactic ablative radiotherapy in 5, 3 or 1 fractions. Dose-limiting toxicity will be recorded as primary endpoint. Acute and late toxicity, local response and local recurrence, and progression-free survival are secondary endpoints. Liquid biopsies will be collected throughout the course of this study from the second fractionation schedule on.

**Discussion:**

Despite its almost universal use in (oligo-)metastatic patients, the level of evidence supporting radical local treatment in general, and stereotactic radiotherapy in particular, is low. This prospective phase I trial will evaluate different SABR regimens for metastases and the differences in immune-stimulatory effects.

**Trial registration:**

The Ethics committee of the GZA Hospitals (B099201732915) approved this study on 05/07/2017. Amendment for translational research was approved on 06/02/2018. Trial registered on Clinicaltrials.gov (NCT03486431) on 03/04/2018 – Retrospectively registered.

## Background

The term oligometastatic disease describes an intermediate state of cancer spread between localized disease and widespread metastases. It is the state in which a patient presents with a limited number of synchronous or metachronous metastases, with the primary tumour either controlled or not. Weichselbaum and Hellman theorized that before development of widespread metastases, malignant cells harbour restricted metastatic potential and occupy only a limited number of sites apart from the primary tumour [1]. Theoretically, aggressive metastasis-directed therapy (MDT) during this time could delay the need to start systemic therapies and/or prolong progression-free survival. The concept of oligoprogression refers to the situation of disease progression in a limited number of locations after an initial response to systemic treatment. This situation is getting more common in the setting of highly innovative systemic therapies, where metastasis-directed therapy could eradicate disease that does not respond to these pharmaceuticals and thus delay the need to change systemic therapy [2].

Stereotactic ablative body radiotherapy (SABR) is one of the MDTs that can be offered to patients with oligometastatic or oligoprogressive disease, who often present with minimal or no associated symptoms [3, 4]. SABR is defined as the precise delivery of highly conformal and image-guided hypofractionated external-beam radiotherapy to extracranial tumours, typically in a single or a few fraction (s), with doses at least biologically equivalent to a conventional radical course of treatment [5]. However, since this is a relatively new technique, information on the optimal scheduling is lacking. Even prospective randomized trials on SABR for oligometastatic disease typically allow different fractionation schedules to be used [6]. This is especially true for non-spine bone and lymph node metastases, where the literature is scarce to non-existent and many different schedules are used, even within a single center [7, 8].

The radiobiological qualities of SABR are potentially useful when treating perceived radioresistant tumours like renal cell carcinoma or malignant melanoma. Radioresistance may be overcome with dose escalation, particularly by increasing the dose per fraction, because of a direct effect on vasculature and cell membranes, rather than through oxygen-dependent DNA damage [9].

Apart from the direct effect of SABR on metastases, there is also emerging evidence that this treatment can improve disease control outside the irradiated volume by stimulating the immune response. This could potentially lead to so-called “abscopal” effects, i.e. response in non-irradiated lesions. A variety of mechanisms, such as increasing TLR4 expression on dendritic cells, increasing priming of T cells in draining lymph nodes, and increasing tumor cell antigen presentation by dendritic cells, is responsible for this effect [10]. Again, it is not clear which fractionation schedule elicits the most robust immune response. For instance, in combination with anti-CTLA-4 immunotherapy, different radiation regimens in two carcinoma models growing in syngeneic mice were compared [11]. Marked differences in induction of tumor-specific T cells and of an abscopal effect were observed. Each regimen had similar ability to inhibit the growth of the irradiated tumor when radiation was used alone. The addition of anti-CTLA-4, however, caused complete regression of the majority of irradiated tumours and an abscopal effect in mice receiving a hypofractionated regimen (3 fractions of 8 Gy) but not in mice treated with a single dose of 20 Gy. An additional fractionated regimen (5 fractions of 6 Gy) was tested, which showed intermediate results. This indicates that a specific therapeutic window may exist for the optimal use of radiotherapy as an immune adjuvant.

An interesting measure of DNA damage in circulating tumor cells (CTCs) is γ-H2AX, a biomarker for radiation-induced DNA double-strand breaks [9]. Apparently, DNA exonuclease Trex1 is induced by radiation doses above 12–18 Gy in different cancer cells, and attenuates their immunogenicity by degrading DNA that accumulates in the cytosol upon radiation. Cytosolic DNA stimulates secretion of interferon-b by cancer cells following activation of the DNA sensor cGAS and its downstream effector STING. Repeated irradiation at doses that do not induce Trex1 amplifies interferon-b production, resulting in recruitment and activation of Batf3-dependent dendritic cells [10]. This effect is essential for priming of CD8+ T cells that mediate systemic tumour rejection (abscopal effect). These data suggest a link between the immune-stimulatory effects of radiation and the DNA damage response.

It therefore seems an opportune moment to compare the most commonly used stereotactic regimens regarding toxicity and efficacy.

## Methods/design

The DESTROY-trial is a non-randomized phase I trial evaluation SABR as treatment for non-spine bone and lymph node metastases. After giving informed consent, patients are included in the DESTROY-trial, which was approved by the Ethics Committee of the GZA Hospitals.

### Objectives

Primary endpointTo determine the maximum tolerated dose (MTD): the maximal tolerated dose will be defined as the dose level below which at least 10 patients present with a dose-limiting toxicity (DLT) at 6 months after SABR.DLT will be defined as any acute grade 3 or 4 toxicity. The DLT observation window is 24 weeks after SABR was delivered. The severity of toxicity will be graded using the Common Terminology Criteria for Adverse Events (CTCAE), version 4.03. For events not reported in the CTCAE version 4.03, the investigator will use the grade or adjectives reported in Table 1.Secondary endpointsTo assess acute and late toxicities following SABR: acute as well as late toxicity will be assessed using the CTCAE version 4.03.To evaluate local response (LR) and local failure (LF): LR will be evaluated by the response evaluation criteria in solid tumors version 1.1 (RECIST v1.1). LF will be scored as an event if an irradiated lesion shows an increase in size of ≥20%, according to RECIST v1.1.To evaluate progression-free survival (PFS): PFS is defined as the time from inclusion to documented disease progression according to RECIST v1.1 or any other clinically relevant definition (e.g. biochemical progression in prostate cancer) or death from any cause.

**Table 1 Tab1:** grade of toxicity

Grade	Adjective	Description
Grade 1	Mild	Does not interfere with patient’s usual function
Grade 2	Moderate	Interferes to some extent with patient’s usual function
Grade 3	Severe	Interferes significantly with patient’s usual function
Grade 4	Life-threatening	Results in a threat to life or in an incapacitating disability
Grade 5	Death	

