### Interventions

A minimum of thirty patients will be included for each dose level. The different treatment regimens and their biological effective doses (BED_10Gy_) and equivalent dose in 2 Gy per fraction (EQD_2Gy_) are presented in Table 2. Calculations for BED_10Gy_ and EQD_2Gy_ are made using an alpha/beta ratio of 10 and 2, respectively. An interval of at least 24 weeks from the first patient treatment to the next patient treatment at each dose level will be respected. In the meantime, more patients will be included in the previous dose level, in an effort to establish the secondary endpoints. In case 1 to 5 patients present with DLT at 6 months after SABR, 30 additional patients will be included at the same dose level.

**Table 2 Tab2:** Fractionation schedules

Level	Fractions	Interval	Dose/fraction	Total	BED_10Gy_	EQD_2Gy_
1	5	48 h	7	35	59.5	78.75
2	3	48 h	10	30	60.0	90
3	1	NA	20	20	60.0	110

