### Statistical analysis

#### Sample size

For each dose level, a minimum of 30 patients will be included. The maximal tolerated dose will be defined as the dose level below which at least 10 patients present with a DLT at 6 months after SABR.

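### The MTD is defined by a fixed count of 10 DLT patients with no denominator, although a dose level may hold 30 or 60 patients, and the sentence places the DLTs below the MTD

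*Protocol article*

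**What the plan says.** The primary endpoint is the MTD. In the protocol article, Objectives states that "the maximal tolerated dose will be defined as the dose level below which at least 10 patients present with a dose-limiting toxicity (DLT"), with assessment half a year post-treatment. The Sample size section gives the same rule: "The maximal tolerated dose will be defined as the dose level below which at least 10 patients present with a DLT". Neither place attaches a denominator, a percentage or a target DLT rate.

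The Interventions section governs how many patients a level holds:

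- **Base size.** "A minimum of thirty patients will be included for each dose level". No maximum is given.
- **Expansion.** "In case 1 to 5 patients present with DLT at 6 months after SABR, 30 additional patients will be included" at that level. Nothing is stated for 6 to 9 DLTs, or for what happens once the expansion is complete.
- **Waiting periods.** "In the meantime, more patients will be included in the previous dose level, in an effort to establish the secondary endpoints".

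The Methods part of the Abstract fixes the overall size: "A total of 90 patients will be included in three different treatment regimens". The Discussion describes the study as a dose-escalation trial with rising dose per fraction.

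**The concern.** A tolerability limit should mean the same thing however many patients a level enrols. A bare count does not, because it becomes stricter as patients are added. Here patients are added because DLTs were few (1 to 5), so the levels that began better are the ones that could face the stricter limit. Two levels could then be ranked by enrolment and not by toxicity, on the trial's only primary decision.

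Two further features of the text make the rule hard to apply. The counts from 6 to 9 lie between the expansion band and the threshold, with no instruction. And the sentence, taken word for word, locates the 10 or more DLTs below the dose called maximum tolerated.

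**Working it through.** **Inputs.** Threshold of 10 DLT patients (Objectives, Sample size). 30 per level, with 30 more after 1 to 5 DLTs (Interventions). Total of 90 in three regimens (Abstract, Methods). The protocol gives no target or expected DLT rate, so true rates of 10% and 20% are assumptions used to show a range.

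**1. The plan's own total.** 3 × 30 = 90. This reproduces the stated figure, but only if no level expands. One expanded level gives 90 + 30 = 120; three give 90 + 90 = 180.

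**2. What the count means as a proportion.** 10/30 = 33.3%; 10/60 = 16.7%. One constant proportion would need 20/60 to match 10/30, or 5/30 to match 10/60. These equivalents are illustrations, not proposals.

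**3. Two reachable outcomes, if expansion patients are pooled** (exact Clopper-Pearson intervals).

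| Course | DLTs/patients | Proportion (95% CI) | Count of 10 reached? |
|---|---|---|---|
| 5/30, expanded, then 5/30 | 10/60 | 16.7% (8.3 to 28.5%) | Yes |
| 9/30, no expansion rule applies | 9/30 | 30.0% (14.7 to 49.4%) | No |

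**4. How often each branch occurs.** Let X1 and X2 be the DLT counts in the first and second 30, each Binomial(30, p).

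| Quantity | p = 10% | p = 20% |
|---|---|---|
| P(X1 = 0) | 0.0424 | 0.0012 |
| P(1 ≤ X1 ≤ 5), expansion | 0.8844 | 0.4263 |
| P(6 ≤ X1 ≤ 9), no stated action | 0.0727 | 0.5114 |
| P(X1 ≥ 10) | 0.0005 | 0.0611 |
| P(1 ≤ X1 ≤ 5 and X1 + X2 ≥ 10) | 0.0391 | 0.2443 |

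The first four rows sum to 1 in each column. The last row is the sum over x = 1 to 5 of P(X1 = x) × P(X2 ≥ 10 − x). Given expansion, the chance of reaching 10 cumulatively is 0.0391/0.8844 = 0.04 at p = 10% and 0.2443/0.4263 = 0.57 at p = 20%.

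So at an assumed 20%, about half of levels would land where the protocol gives no instruction. A level that expands would reach the threshold more often than not, whereas 30 patients alone reach it with probability 0.06.

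**5. Direction of the sentence.** Dose per fraction rises from 7 to 10 to 20 Gy over levels 1 to 3 (Table 2). If 10 or more DLTs occur below level k, then the level named as MTD lies above a level that met the toxicity count. That conflicts with the term maximum tolerated dose in an escalation design.

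**The case against.** Several points on the other side carry weight.

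- **Pooling is not stated.** If the count applied only to the first 30 patients, the 10/60 case would disappear, and a total of 90 with a minimum of 30 per level fits that reading. But no text limits the count to the first 30. On that reading, the 30 patients added because DLTs occurred would have no part in the MTD decision. The 10/60 result therefore stands as conditional on pooling.
- **Waiting-period patients.** The protocol says they are enrolled for the secondary endpoints, which points away from counting them towards the MTD. No calculation here includes them. What remains is that their exclusion is not explicit.
- **Does 9/30 pass?** A reader might infer that such a level is declared tolerable. The document does not say so: 9/30 is short of the count, and no action follows. For the same reason one cannot conclude that the rule hardly distinguishes a 20% from a 25% DLT rate. Treating 6 to 9 as acceptable gives flagging probabilities of 0.31 and 0.36; treating it as not tolerable gives 0.82 and 0.96. The contrast depends on how the gap is filled.
- **Low expected toxicity.** The only grade 3–4 rates quoted in the Discussion are 0 to 4%, for renal cell carcinoma metastases. At 4%, reaching 10 of 60 has probability of about 0.0001, so the threshold would rarely matter. Expansion would still be likely (0.71 at 4%), and the conflict with 90 patients remains.
- **Direction of the wording.** The intended sense can be guessed, and it is unlikely that the sponsor would name the wrong level in practice. That makes this part a drafting correction, but the sentence appears twice and defines the primary endpoint.

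**Conclusion.** The point holds. As written, the primary rule is a count without a denominator, applied to levels that may hold 30 or 60 patients, so it corresponds to 33.3% or 16.7% depending on enrolment. If expansion patients are pooled, a level at 16.7% can reach the limit while one at 30.0% does not.

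The missing instruction for 6 to 9 DLTs needs no pooling assumption. It affects 0.51 of levels at an assumed true rate of 20% and 0.07 at 10%. The mismatch between the expansion rule and the total of 90 depends on no assumed rate, and the literal direction of the definition conflicts with an escalation trial.

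The documents do not support saying that 9/30 is declared tolerable, that 10/60 necessarily fails, or that the wrong level will be chosen. Because the defect lies in the primary decision rule and can be corrected in the text, it should be corrected.

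**What to change.** Reconcile the Abstract (Methods), Objectives, Interventions and Sample size sections:

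1. State the sponsor's own threshold as a DLT proportion of a defined denominator, in a form that holds at both 30 and 60 patients.
2. Say whether the 30 expansion patients enter the count, and whether the patients added during waiting periods do.
3. Reconcile the 6 to 9 DLT range with the expansion band and the threshold.
4. Reconcile the total of 90 with the possibility of expansion.
5. Reword the definition in both places so that its direction is unambiguous.
6. Report each level's DLT proportion with an exact 95% CI.

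The threshold and the clinical rule are for the sponsor to set; none is proposed here. The cost is a wording amendment with no new procedures. It adds no patients beyond those that the expansion rule already implies, though stating that number openly may show a total above 90.

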#### Data analysis

All data will be prospectively collected. Electronic case report forms will be used; database will be excel-based and Access-based. Statistics will be carried out using the latest version of SPSS. The primary endpoint MTD will be evaluated at 6 months after the end of SABR. The incidence of acute and late toxicity will be recorded. Chi-square test will be used to find out the significance of results. Disease free survival will be calculated using Kaplan Meier actuarial analysis. Survival times are defined from the date of start of the treatment until an event or last follow up.

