SABR is also often used for treating metastases from radioresistant tumors like renal cell carcinoma or malignant melanoma. Radioresistance may be overcome with dose escalation, particularly by increasing the dose per fraction [9]. A systematic review of Kothari ea. evaluating the use of SABR found excellent LC rates and low rates of toxicity for intracranial and extracranial metastatic renal cell carcinoma [26]. They reported a weighted one-year LC rate of 86% and grade 3–4 toxicities ranging from 0 to 4%. In the setting of oligometastasized malignant melanoma, there is less clinical data available. Nevertheless, a prospective study showed high rates of complete response and durable metastasis control with SABR for extracranial metastases of malignant melanoma, including bone and lymph node metastases [27]. Both for malignant melanoma and for renal cell carcinoma, LC rates achieved are comparable to those obtained with SABR for other histologies, suggesting a dominant mechanism of in vivo tumor ablation that overrides intrinsic differences in cellular radiosensitivity between histologic subtypes [28].

The concept of a risk-adapted approach for SABR fractionation regimens, using smaller fraction sizes for tumor locations that overlap with organs at risk for toxicity, has gained widespread acceptance. This concept is based on the assumption that fractionation relatively decreases the EQD2 for normal tissues. The results of this dose escalation trial, with increasing dose per fraction, can help to improve the risk-adapted approach for non-spine bone and lymph node metastases. Also important in this regard is the alpha/beta ratio of 10 used in the BED calculations, which is an estimate of the general alpha/beta ratio of tumor metastases. However, the available clinical data support the use of a lower alpha/beta for renal cell carcinoma, breast or prostate cancer, which would lead to a higher BED.

To keep the study protocol accessible to most metastasized patients, there is no limitation on the use of concurrent systemic treatment, but this gives a possible increase in acute or late toxicity.

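### The DLT definition stops at grade 4, so a fatal toxicity with no earlier grade 3–4 event counts as no DLT, and its qualifier 'acute' is left undefined beside a 24-week window

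*Protocol article*

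**What the plan says.** The Objectives section defines the primary endpoint event: "DLT will be defined as any acute grade 3 or 4 toxicity". The next sentence gives the period: "The DLT observation window is 24 weeks after SABR was delivered". Toxicity is graded by CTCAE version 4.03, with Table 1 for events that CTCAE does not cover. Table 1 runs from grade 1 to grade 5 and lists death as grade 5, separate from the life-threatening events of grade 4.

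The secondary endpoints name two categories of toxicity: "acute as well as late toxicity will be assessed using the CTCAE version 4.03". The article gives no time boundary between them.

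Two decisions use the DLT count. In Objectives, repeated under Sample size, the MTD is "the dose level below which at least 10 patients present with a dose-limiting toxicity (DLT) at 6 months after SABR". In Interventions: "In case 1 to 5 patients present with DLT at 6 months after SABR, 30 additional patients will be included at the same dose level". On numbers, Sample size says "For each dose level, a minimum of 30 patients will be included". Data analysis adds that "The primary endpoint MTD will be evaluated at 6 months after the end of SABR".

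On other causes of toxicity, the Discussion says that "there is no limitation on the use of concurrent systemic treatment, but this gives a possible increase in acute or late toxicity".

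**The concern.** An MTD endpoint should count the worst toxicity. Here the definition closes the grade range at 4, although the article's own scale continues to 5. Read as written, a patient who has a grade 3 toxicity and recovers is a DLT, and a patient who dies of toxicity without an earlier qualifying event is not. The error runs in the unsafe direction, because a level looks better tolerated than it was.

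The second problem is the word 'acute'. It is an extra condition next to a 24-week window, in a document that also recognises late toxicity. Without a boundary, two investigators could class the same grade 3 event in month 5 differently, and the primary count would follow that choice.

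At stake are the two decisions that depend on the count: adding 30 patients to a level, and the MTD.

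**Working it through.** **Planned size.** Three levels × 30 patients = 90, which matches the total in the Abstract. The article gives no target DLT rate, alpha or power, so there is no power figure to reproduce. The point disputes a definition, and the sample size stays the same.

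**Grade range, side by side.**
- DLT definition: grades 3 and 4.
- Table 1: grades 1 to 5, with death as grade 5.
- No other section of the article adds grade 5 to the DLT.

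A fatal toxicity is therefore outside the definition. The rules count patients, so a death is missed only if that patient had no earlier acute grade 3–4 event. Such a patient is called fatal-only below.

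**How likely is a fatal-only patient?** The chance of at least one among n = 30 is 1 − (1 − p)^30. The rates p are assumptions; the article gives none.
- p = 0.5%: 1 − 0.995^30 = 14%
- p = 1%: 1 − 0.99^30 = 26%
- p = 2%: 1 − 0.98^30 = 45%

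**Would one such patient change a decision?** Suppose one of 30 is fatal-only and the other 29 each have a countable DLT with probability q. The Discussion cites grade 3–4 toxicity of 0 to 4% for SABR of metastatic renal cell carcinoma, which gives a range for q.

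*Expansion (0 versus 1).* The omission matters if the other 29 have no DLT, which has probability (1 − q)^29.
- q = 0: 100%
- q = 2%: 0.98^29 = 56%
- q = 4%: 0.96^29 = 31%

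*MTD (9 versus 10).* The omission matters if exactly 9 of the other 29 have a DLT, which has probability C(29,9) q^9 (1 − q)^20.
- q = 4%: about 0.0001%
- q = 30% (assumed): 16%

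At the toxicity rates that the article cites, the expansion decision is the one realistically exposed. The MTD decision is exposed only if toxicity is far higher.

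**'Acute' beside the window.** Two readings fit the text.
- 'Acute' means any onset within the 24 weeks. Every grade 3–4 event in the window then counts, and the word adds nothing.
- 'Acute' means something shorter. A severe event late in the window is then inside the window but outside the definition.

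The article does not choose between them. To show what the choice could be worth, assume a true severe-event rate of 30% and let a share go uncounted because the events are grade 5 or not called acute. P(at least 10 of 30) then changes as follows.
- None uncounted (30%): 41.1%
- A quarter uncounted (22.5%): 11.7%
- Half uncounted (15%): 1.0%

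The 30% and both shares are illustrations, not figures from the article.

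**Window wording.** The window is 24 weeks (24 × 7 = 168 days) in one sentence of Objectives. The DLT or MTD is placed at 6 months (365.25 / 2 ≈ 183 days) in Objectives, Interventions, Sample size and Data analysis. The gap is about 15 days.

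**The case against.** The strongest reply is that the window sentence directly follows the DLT definition and most naturally says how long events are counted. Table 3 fits this, since it places the 3- and 6-month visits within the trial period and lists later visits as follow-up. On that reading 'acute' simply means within the window. This stands far enough that a reader may not conclude that severe events in months 4 to 6 are excluded: no section classes them as late. What remains is an undefined term in the primary endpoint.

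The reply also holds on timing. The 24 weeks and 6 months are nominal equivalents tied to the same visit, and no decision is shown to turn on 15 days. A reader might take a DLT at 6 months to mean toxicity still present at that visit, but the stated observation window speaks against it.

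A further inference is tempting: because 'any' toxicity counts and systemic treatment is unrestricted, unrelated events could drive the MTD. The documents do not support calling this an error. Counting events whatever their cause is a defensible conservative choice, and the Discussion discloses the possible added toxicity. The sizes do not carry the inference either. At assumed background rates of 3%, 7.5% and 10%, P(at least 10 of 30) from background alone is about 0.000001%, 0.004% and 0.05%. Background rates of 20% and 30% give 6.1% and 41.1%, but nothing in the article points to such rates. Background events would often trigger the expansion (60%, 90% and 96% at the same three rates). However, SABR toxicity at the cited 4% alone does so with probability 1 − 0.96^30 = 71%, and the consequence is a cautious one.

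None of these replies answers the grade 5 gap.

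**Conclusion.** The omission of grade 5 is wrong as written and needs correction. It follows from the definition and Table 1 alone and rests on no assumed rate. It affects only patients whose fatal toxicity was not preceded by a counted event. One such patient in a level of 30 would reverse the expansion decision with probability 31% to 100% if the other patients' grade 3–4 rate lies in the cited range of 0 to 4%. It could reverse the MTD decision only in a level that otherwise stands at 9 DLTs, which is very unlikely at those rates. How often fatal-only patients occur is unknown; the 14% to 45% above rests on assumed rates of 0.5% to 2%.

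The undefined 'acute' is an inconsistency to be resolved, not a demonstrated exclusion. The two expressions of the window are a wording mismatch to be tidied in the same edit. The lack of an attribution rule is not part of the defect.

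**What to change.** In Objectives, amend the primary endpoint so that any toxicity of grade 3 or higher, including grade 5, is a DLT, counted once per patient. Reconcile 'acute' with the observation window so that every qualifying event with onset inside the window counts.

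Use one expression for the window in Objectives, Interventions, Sample size and Data analysis, and say that the patient had a DLT by the end of the window rather than at 6 months.

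As an optional supportive analysis, report the DLT proportion with and without concurrent systemic treatment. Whether the primary count should require attribution to SABR is for the sponsor to decide and state.

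The cost is a wording amendment. The planned sample size and the treatment schedules are untouched. The DLT count may rise slightly, which could bring an expansion that the present wording would not trigger.

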Even though the data are still not sufficient to be able to routinely recommend SABR, the high LC rates and low toxicity rates observed after SABR in patients with oligometastatic disease and in patients with radioresistant metastases justifies continued exploration of strategies for ablative dose delivery within research protocols. To date, we do not have any clear results that demonstrate the benefit of one type of dose or fractioning over another. The aim of this prospective phase I trial is to establish the optimal regimen of SABR for non-spine bone and lymph node metastases, regarding acute and late toxicity as well as efficacy.

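### The MTD counts only acute toxicity to 24 weeks, and late toxicity, which the stated aim includes, is compared with no fixed time point although the last level has the shortest follow-up

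*Protocol article*

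**What the plan says.** **Primary endpoint.** Under Objectives, "DLT will be defined as any acute grade 3 or 4 toxicity", and "The DLT observation window is 24 weeks after SABR was delivered". Objectives and Sample size define the MTD by a count of at least 10 patients with DLT at 6 months. Data analysis places the MTD evaluation at 6 months after SABR ends. Under Interventions, 1 to 5 patients with DLT at 6 months lead to 30 more patients at the same level.

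**Dose levels.** On Table 2, "Calculations for BED_10Gy_ and EQD_2Gy_ are made using an alpha/beta ratio of 10 and 2, respectively". In the Discussion's paragraph on risk-adapted fractionation, "This concept is based on the assumption that fractionation relatively decreases the EQD2 for normal tissues".

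**Late toxicity.** It is a secondary endpoint, graded by CTCAE 4.03. Table 3 registers toxicity at every follow-up visit, for life. Data analysis says that acute and late incidence will be recorded and names a chi-square test. It gives no time at which levels are compared.

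**Aim.** The abstract says that the trial determines a regimen of choice. The Discussion closes by saying that the aim "is to establish the optimal regimen of SABR for non-spine bone and lymph node metastases, regarding acute and late toxicity as well as efficacy".

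**The concern.** The quantity that changes most across the levels in biological terms is the low-alpha/beta equivalent dose, which the article itself connects with normal tissue. The only rules that turn toxicity into a decision stop at 24 weeks and count only acute events. A severe event at month 9 enters no stated rule, yet late toxicity is part of the stated aim.

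The secondary endpoint could fill this gap, but the comparison as described is not a fair one. Without a time point, incidence depends on how long each level has been followed, and the level opened last has been followed for the shortest time. At stake is whether the single-fraction level looks acceptable on late toxicity partly because its patients have had less time to develop it.

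**Working it through.** **1. Reproduce Table 2.** The rows (level, fractions, interval, dose per fraction, total, BED, EQD2) read "1 5 48 h 7 35 59.5 78.75", "2 3 48 h 10 30 60.0 90" and "3 1 NA 20 20 60.0 110". Let n be the number of fractions and d the dose per fraction.

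BED at alpha/beta 10 = n·d·(1 + d/10):
- Level 1: 35 × 1.7 = 59.5
- Level 2: 30 × 2.0 = 60.0
- Level 3: 20 × 3.0 = 60.0

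EQD2 at alpha/beta 2 = n·d·(d + 2)/(2 + 2):
- Level 1: 35 × 9/4 = 78.75
- Level 2: 30 × 12/4 = 90
- Level 3: 20 × 22/4 = 110

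All six entries reproduce.

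**2. Change from level 1 to level 3.**
- BED at alpha/beta 10: 60.0/59.5 = 1.008, or +0.8%.
- EQD2 at alpha/beta 2: 110/78.75 = 1.397, or +39.7%.

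**3. Sensitivity to alpha/beta.** EQD2 = n·d·(d + a)/(2 + a), where a is the alpha/beta ratio:

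| a | Level 1 | Level 2 | Level 3 | Level 3 vs 1 |
|---|---|---|---|---|
| 10 | 49.58 | 50.0 | 50.0 | +0.8% |
| 3 | 70.0 | 78.0 | 92.0 | +31.4% |
| 2 | 78.75 | 90 | 110 | +39.7% |
| 1.5 | 85.0 | 98.6 | 122.9 | +44.5% |

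The values 3 and 1.5 are assumptions, used only to show the range. The pattern (flat at 10, rising at low values) does not depend on the exact choice.

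**4. What each rule can see.**

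| Element | Acute grade 3–4 to 24 weeks | Late, or after 24 weeks |
|---|---|---|
| MTD | yes | no |
| Expansion by 30 patients | yes | no |
| Secondary toxicity analysis | yes | yes, no time point |
| Stated aim | yes | yes |

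**5. Follow-up by level.** Interventions requires an interval of at least 24 weeks and fills the wait with further patients at the previous level. If that interval separates the first treatments at successive levels, the first level-3 patient starts at least 2 × 24 = 48 weeks after the first level-1 patient. At any single data cut, level 3 then tends to have the least follow-up. A cumulative proportion can only grow with time, so a crude chi-square tends to understate late toxicity at level 3 relative to level 1. The article gives no late event rate, so the bias has a direction but no computable size.

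**The case against.** The strongest defence has five parts.

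- **Dose is not risk.** A reader might infer that the risk of late harm rises by 40%. The documents do not support this. The 39.7% is a calculated equivalent of the prescribed dose, and no dose–risk relation is given. Organs at risk have their own published constraints, and target coverage may be given up to meet them, so the dose to a constrained organ cannot be read from Table 2. This stands, although normal tissue inside the target is not covered by it.
- **Late tissue is not named.** The article does not assign alpha/beta 2 to late-responding tissue. The Discussion speaks of normal tissues generally and also supports lower ratios for renal cell, breast and prostate tumours. One therefore cannot say that the trial, by its own figures, escalates late effect alone. Low-alpha/beta effects that appear early and are graded as acute can still count as DLT. This stands.
- **The MTD might be the same anyway.** A reader might infer that the 24-week limit by itself would reverse the MTD. The rule needs at least 10 patients, and fewer than 10 late events would not reach that number alone. The cited non-spine bone studies saw no late toxicity of grade 3 or greater, and the renal cell review reports grade 3–4 rates of 0 to 4%. The documents do not show that the MTD would change.
- **Late toxicity is not ignored.** It is followed for life and analysed, and nowhere is the regimen said to be chosen on the MTD alone. This stands, and it moves the weight of the point to how the late comparison is made.
- **An article condenses the protocol.** How endpoints are weighed may be set out in the full document. That answers a charge of omission. It does not answer the stated definitions, which leave late events out of the MTD, or the stated test, which as described would compare unequal follow-up.

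**Conclusion.** The point holds in a limited form. By the article's definitions, toxicity classed as late or arising after 24 weeks cannot enter the MTD or the expansion rule, while the aim names late toxicity. Across the levels the alpha/beta-10 dose changes by 0.8% and the alpha/beta-2 equivalent dose by 39.7% (31% to 45% for ratios of 3 to 1.5). An acute endpoint alone is therefore a thin basis for a regimen of choice. The practical defect is the late comparison: an undated chi-square on levels opened in sequence favours the last level.

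This rests on the linear-quadratic formulas that reproduce Table 2, on the article's link between EQD2 and normal tissues, and on reading the chi-square as applied to crude incidence. It does not show that late harm will differ between levels, or that the MTD is wrong as a 24-week result.

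**What to change.** 1. In Objectives, Sample size and Data analysis, call the primary result an acute (24-week) MTD. The DLT window itself need not change.
2. State that the regimen of choice also rests on late toxicity of grade 3 or higher, compared across levels at one common time after SABR, for example 12 months. Table 3 already has a visit then, whether its quarterly first-year visits are counted from SABR or from the 6-month visit (6 + 3 + 3 = 12).
3. Replace the undated chi-square for late toxicity with cumulative incidence at that time, treating death as a competing event. Only a life expectancy under 6 months is excluded, so some patients may die before month 12.
4. Reconcile Objectives, Interventions, Data analysis and the closing Discussion on how late toxicity informs the conclusion. Any limit is for the sponsor to set.

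**Cost.** The change is wording and one analysis method, since the visits and toxicity registration already exist. Level opening is not delayed. The final statement on level 3 comes about 6 months later (12 months instead of 6).
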